### 2.2.3 Insulin Sensitivity and Secretion

The efficacy and durability of the successful treatment of T2DM is determined to a great extent by the ability of a specific intervention to ameliorate insulin resistance and prolong or

restore effective beta cell function. There is significant information available on the natural history of insulin resistance and secretion, and on the effect of various treatment regimens on secretion and sensitivity in adult patients with T2DM. Little is currently known about these natural history and treatment issues in affected children and youth. In particular, significant questions remain about the impact of advancing pubertal status on insulin resistance and beta cell function in pediatric patients with T2DM. Therefore, an important component of TODAY is to determine (1) the influence of baseline insulin sensitivity and secretion on the response to therapy and (2) the effect of each therapy on the progression of changes in insulin sensitivity and secretion.

To determine the optimal assessment of insulin sensitivity and secretion in this large cohort of study patients, a number of factors were taken into consideration. The glucose clamp technique and the frequently sampled intravenous glucose tolerance test with minimal model analysis are considered the 'gold standard' for determination of insulin sensitivity and secretion. However, these are labor intensive, time consuming, and costly procedures that are not easily implemented in large clinical trials. A number of simpler methods have been developed that are preferable in the context of large clinical trials such as TODAY. The oral glucose tolerance test (OGTT), homeostasis model assessment (HOMA), and the quantitative insulin sensitivity check index (QUICKI) are used to compare insulin secretion and sensitivity among the three treatment groups. Use of these multiple measures helps compensate for not using the 'gold standard' measures as listed above. Values of glucose and insulin/C-peptide derived from the OGTT, when combined with anthropometric parameters, can predict insulin sensitivity and secretion indices derived from clamp measurements with reasonable accuracy [Breda et al. 2002; Stumvoll et al. 2000; Guzzaloni 2002]. The OGTT-derived equations that assess insulin sensitivity take into account BMI, 120-minute insulin levels, and 90-minute glucose values. The assessment of first phase insulin secretion is done with the fasting and 60 minute insulin concentrations.

A number of indices based on fasting measurement of glucose and glucose regulating hormones such as insulin (including C-peptide) and proinsulin have also been proven to closely correlate with corresponding clamp-derived indices of insulin sensitivity and secretion in diverse pediatric populations [Bonora et al. 2000; Hermans et al. 1999; Katz 2000; Guzzaloni 2002; Uwaifo 2002]. Since it is easy to obtain fasting blood tests, evaluation of these measurements to assess insulin sensitivity and secretion is ideal for a large clinical trial. HOMA-R (resistance) and B (secretion) are calculated using a computer-based model solution. QUICKI is calculated as  $1/(\log[I_0] + \log[G_0])$ .

Insulin sensitivity and secretion are determined with fasting glucose, insulin, C-peptide, and proinsulin levels, OGTT, HOMA, and QUICKI at baseline, 6 months, annually, primary endpoint, and end of study and are compared among the three treatment arms.

#### 2.2.4 Body Composition

In children and adolescents, obesity is associated with insulin resistance, hypertension, dyslipidemia, non-alcoholic fatty liver disease (NAFLD), and left ventricular hypertrophy. The development of insulin resistance during puberty is most closely correlated to fat mass, independent of insulin, sex steroids, leptin, or IGF-1 status [Roemmich et al. 2002]. Obesity causes an increase in intramuscular triglyceride content in adolescents relative to lean controls that is associated with a decrease in insulin sensitivity [Sinha et al. 2002]. Weight loss in overweight adolescents improves both insulin sensitivity [Kay et al. 2001] and blood pressure [Brownell et al. 1983]. However, there are scarce data describing the effects of weight loss on these parameters in children or adolescents with diabetes. An important secondary outcome of TODAY is the investigation of whether weight loss, in particular a decrease in adiposity, improves glycemic control, insulin sensitivity, cardiovascular risk

version 1.9, January 24, 2011

factors, and blood pressure in children and adolescents with T2DM as it does in the adult diabetes population and in overweight adolescents. An accurate measurement of body fat is essential during this trial to determine the effectiveness of the lifestyle intervention, which focuses on weight loss, as well as to help clarify the mechanism of effect.

Overweight status and body composition are assessed by standardized anthropometric measurements (height, weight, BMI) as well as waist circumference, and abdominal height measured laterally with the patient supine [Pouliot et al. 1994]. Percent body fat and fat distribution are measured by dual-energy X-ray absorptiometry (DXA). A cross-calibration study of different body composition techniques versus DXA in children has shown that skinfold thickness measurements, bioelectrical impedance, and various combinations of anthropometric measures are highly inaccurate when compared to DXA [Goran et al. 1996]. Therefore, DXA is the main measure to assess the effect of the three treatment arms on adiposity. DXA (with pediatric software as appropriate) uses a three-compartment model of total body fat mass, bone mineral mass, and non-bone lean mass. This is of particular importance in a multi-ethnic study since bone mineral content and lean tissue mass differ by gender and ethnicity [Ellis et al. 1998; Cote and Adams 1993].

Height and weight are measured at each study visit. Participants undergo other anthropometric measurements and DXA analysis of body composition at baseline, six months, two years, primary endpoint, and end of study; results are compared among the three treatment arms.

In addition, biological parent height and weight are collected at baseline in order to evaluate the predictive effect of parent BMI on outcomes. Height and weight are collected from the family support person (FSP) on an annual basis in order to determine the effect of FSP weight loss or participation in the lifestyle intervention with participant anthropometrics and body composition.

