Because of these difficulties, investigators have resorted to predicting  $\text{VO}_2$  max. The most popular methodologies to predict  $\text{VO}_2$  max in children have utilized cycle ergometry to determine the physical work capacity or PWC [Boreham 1990]. These tests involve obtaining heart rates at three submaximal workloads, plotting these heart rates against the workload, extrapolating to determine the workload at a given heart rate or at maximal heart rate, and then converting that maximal workload to oxygen uptake. Participants sit quietly while their heart rate is measured, until they have adapted to the laboratory and their heart rate is stable. They then begin the multistage fitness test, beginning at 150 kpm and increasing in 150 kpm increments every three minutes until a heart rate of 160 bpm is reached. The work required to produce a heart rate of 160 bpm is used to extrapolate the PWC at a heart rate of 170 bpm. This prediction of  $\text{VO}_2$  max has several advantages. First, the PWC equipment and space needs are modest. Second, the PWC can be administered in 12-15 minutes and requires only the measurement of heart rate. Third, the PWC is ideal to use in a test-retest protocol since learning, practice, or training have little effect on its results.

In this protocol, participants undergo PWC 170 testing at baseline, six months, two years, primary endpoint, and end of study, and the effects of the three treatment arms on fitness are compared.

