# 8 Statistical Considerations

## 8.1 Sample Size

The primary outcome for the TODAY study is time to treatment failure, defined as persistently elevated HbA1c levels ( $\geq 8.0\%$  for 6 months) or the inability to be weaned safely from temporary use of insulin therapy. No published data exist that allow estimation of the rate of occurrence. From unpublished data collected in the participating clinical centers, it is estimated that between 10-20% of children will have an HbA1c above the threshold by the end of each 6 month period, beginning at the end of the first year. The following assumptions were used to determine the sample size goal for TODAY:

- Primary outcome is time to failure as defined above.
- Eligible patients are randomized evenly to one of three treatment arms and followed for an additional two years following close of randomization.
- Rate of treatment failure within treatment group is constant over time.
- Treatment failure in the reference group (metformin alone) is at least 10% per six-month period, beginning at the first annual visit.
- There is a reduction of at least 40-50% in the treatment failure rate in one of the more intensively treated groups.
- Ten percent of patients are lost to drop-out during each 6 month period.
- The type I error rate ( $\alpha$ ) is 0.05 (two-sided) with a Bonferroni adjustment [Miller 1981] for three pair-wise comparisons of the three treatment groups.

Given these assumptions, if 10% of the metformin group has an HbA1c above the threshold, 250 participants per arm provides at least 90% power to detect a 50% reduction in the treatment failure rates in at least one combination therapy group (i.e., 5% with HbA1c above threshold during a six-month period). If 20% of the metformin group has an HbA1c above the threshold, 250 participants per treatment arm provides at least 90% power to detect a 40% reduction in hazard rates in at least one of the combination therapy groups (i.e., 12% failing during a six-month period). Therefore, 250 participants per group are recruited.

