Life-table analysis assesses the risk of the first event in time. Some processes, however, involve recurrent events such as the back-and-forth between elevated and normal blood pressure. For these recurrent events, the family of statistical models based on the theory of counting processes are applied [Fleming and Harrington 1991].

Longitudinal data analysis techniques are used to analyze repeated measures data (e.g., glycemia, fasting lipids, blood pressure, physical activity, quality of life). These include: (1) analyses of the point prevalence of a discrete characteristic (e.g., hypertension) at successive repeated visits over time [Lachin and Wei 1988]; (2) multivariate rank analyses of quantitative (e.g., 2 hour OGTT) or ordinal (e.g., the Child Health Questionnaire subscales) measures over successive visits [Wei and Lachin 1984]; (3) the parametric linear random effects model of Laird and Ware [1982] to compare participant slopes over time (e.g., rate of change in fasting glucose) under linearity and normality assumptions; and (4) techniques developed by Liang and Zeger [1986] to compare participant slopes under a generalized linear models framework.

- *Interim analysis:* The Lan-DeMets [1983] spending function approach is used to adjust the probability of a type I error for testing the primary outcome when interim ‘looks’ of the data are taken by the Data Safety Monitoring Board. The spending function corresponding to an O’Brien and Fleming [1979] boundary are used. The Lan-DeMets procedure is flexible, in that the number of looks does not have to be specified in advance and the time interval between looks does not have to be the same throughout TODAY. The rate at which the type I error is spent is a function of the fraction of total information available at the time of the interim analysis (i.e., information time). For an interim analysis using the logrank test (i.e., time to confirmed treatment failure), the information time is the fraction of the total number of confirmed treatment failures to be accrued in the entire TODAY. Since the total number of failures to be accrued is unknown, an estimate of the information time is based on the fraction of total patient exposure [Lan and Lachin 1990].

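### No method named in Section 8.2 for continuous secondary outcomes conditions on the participant's own baseline value, although that value is collected

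*Protocol*

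**What the plan says.** Three sections of the protocol schedule a baseline and later measurements of the same quantity and then announce a comparison of arms.

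- Section 2.2.3 (insulin sensitivity and secretion): baseline, 6 months, annually, "primary endpoint, and end of study and are compared among the three treatment arms".
- Section 2.2.4 (DXA and anthropometry): baseline, six months, two years, "primary endpoint, and end of study; results are compared among the three treatment arms".
- Section 2.2.7 (PWC170): baseline, six months, two years, primary endpoint and end of study, and "the effects of the three treatment arms on fitness are compared".

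Section 8.2 then lists the techniques for repeated measures. One is for the prevalence of a discrete characteristic. For quantitative or ordinal data it names "multivariate rank analyses of quantitative (e.g., 2 hour OGTT) or ordinal (e.g., the Child Health Questionnaire subscales) measures over successive visits"; the title of the reference cited for this describes two-sample tests. The other two compare participants' slopes over time: a linear random effects model, with linearity and normality stated as its assumptions, and a generalized linear model approach. The list does not mention the baseline value as a covariate. Covariates appear in Section 8.2 only for the time-to-event outcomes.

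**The concern.** Participants are 10 to 17 years old and can be expected to differ widely in size, pubertal stage and fitness. A large part of the spread in a follow-up value of body fat, an insulin index or PWC170 is then likely to be spread that was already there at baseline. An arm comparison of raw visit values leaves it in the error term. A comparison of slopes removes it, but summarises the treatment effect as a straight line.

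Section 2.2 says the secondary outcomes are there to help interpret the primary result, and Section 2.2.4 makes DXA the main measure of the treatments' effect on adiposity. An imprecise comparison could be read as absence of a mechanism when the analysis had little chance of showing one.

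**Working it through.** **What the protocol states.** It gives no power or precision figure for any continuous secondary outcome. Its only such figures are for the primary outcome, for example that "250 participants per arm provides at least 90% power to detect a 50% reduction in the treatment failure rates". With exponential failure and drop-out, three-year accrual and a significance level of 0.05/3, that scenario gives 97.6% power if failures start at once and 88.0% if they start after 12 months. The second scenario gives 98.1% and 91.0%. The stated 90% is thus reproduced to within about 2 points and has no bearing here. Section 8.1 contributes only the numbers of participants.

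**Inputs.**
- 250 per arm and 10% drop-out per six months (Section 8.1): 250 × 0.9 = 225 at month 6 and 250 × 0.9⁴ = 164 at month 24.
- Fixed visits for DXA and PWC170 at 0, 6 and 24 months (Sections 2.2.4 and 2.2.7).
- Correlation r between baseline and follow-up: not in the protocol; assumed 0.5 to 0.8.
- Two-sided 5%, one pair of arms, equal variances and the same correlation between any two visits: assumptions.

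**Check 1: raw visit values against baseline adjustment.** Per participant, in SD² units, the variance is 1 for a raw value and 1 − r² after adjustment, so the raw comparison is inflated by 1/(1 − r²). At r = 0.7 this is 1/0.51 = 1.96, about double. Detectable difference with 80% power = (1.960 + 0.842) × √(2/n) × √(1 − r²). With n = 164:

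| | Raw | r = 0.5 | r = 0.7 | r = 0.8 |
|---|---|---|---|---|
| Detectable difference (SD) | 0.309 | 0.268 | 0.221 | 0.186 |
| Power for 0.25 SD | 62% | 74% | 89% | 97% |

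These are normal-theory figures, used as a stand-in for the rank test at one visit.

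**Check 2: slopes against baseline adjustment, variance only.** With visits at 0, 0.5 and 2 years the sum of squared deviations of time is 2.167. The variance of the two-year difference implied by the slopes is 2 × 4(1 − r)/2.167, and by ANCOVA at month 24 it is 2(1 − r²), each divided by n.

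| r | Slopes | ANCOVA | Saving |
|---|---|---|---|
| 0.5 | 1.846 | 1.50 | 19% |
| 0.6 | 1.477 | 1.28 | 13% |
| 0.7 | 1.108 | 1.02 | 8% |
| 0.8 | 0.738 | 0.72 | 2% |

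**Check 3: slopes when the effect is not linear.** Section 4.4.4 schedules lifestyle sessions weekly for months 1 to 6, every two weeks to month 12, monthly to month 24, then quarterly. Take r = 0.7 and 164 per arm. The standard errors are √(1.108/164) = 0.0822 for slopes and √(1.02/164) = 0.0789 for ANCOVA.

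- Effect growing linearly to 0.25 SD at month 24: slopes Φ(0.25/0.0822 − 1.960) = 86%; ANCOVA Φ(0.25/0.0789 − 1.960) = 89%.
- Effect of 0.25 SD reached by month 6 and sustained: the fitted slopes imply a two-year difference of 2 × 0.25 × (1.167 − 0.333)/2.167 = 0.192 SD. Power is Φ(0.192/0.0822 − 1.960) = 65% for slopes and 89% for ANCOVA at month 24. At r = 0.5 the pair is 44% and 74%; at r = 0.8 it is 82% and 97%.
- Effect of 0.25 SD at month 6, halved by month 24: slopes 11%; ANCOVA 96% at month 6 (225 per arm) and 35% at month 24.

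**The case against.** A reader might infer that the protocol compares these measures on follow-up values alone, or ties them to unadjusted rank tests. It does neither. Sections 2.2.3, 2.2.4 and 2.2.7 list the measurement times, baseline included, and say that arms are compared. Section 8.2 assigns no method to DXA, HOMA/QUICKI or PWC170; its example for the rank analysis is the 2 hour OGTT. The Kruskal-Wallis test is named only for baseline characteristics.

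A reader might also infer that baseline goes unused throughout. That is too strong. A slope model can take the baseline visit as its first point, and the random intercept absorbs stable differences between participants. The generalized linear model framework accepts covariates. Section 2.2.3 names baseline insulin sensitivity and secretion as a possible influence on response. The list of techniques is open, so it does not exclude ANCOVA.

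It is also fair to say that the model for each secondary outcome is usually settled in a statistical analysis plan, which is not at hand, and that randomization protects validity either way.

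Most of this stands and limits the point. It does not remove it, because Section 8.2 does more than stay silent: it names methods for quantitative measures, none of them stated to condition on baseline. The OGTT, its own example for the rank option, has a baseline measurement in the Section 5.1 schedule. The slope options match baseline adjustment closely only when the effect is roughly linear.

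**Conclusion.** The point holds in a narrow form, as a low-priority improvement. Section 8.2 names a rank analysis and slope comparisons for quantitative repeated measures, and no named method conditions on the participant's own baseline.

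The size depends on which option is used. Against the rank option on raw visit values the gain is substantial if the correlation is 0.5 or more: a variance reduction of 25% to 64% for r from 0.5 to 0.8. Against slopes with a linear effect it is small. Against slopes with an early, sustained effect it is again material, and the tapering lifestyle program makes such a course plausible.

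All figures rest on assumed correlations, a common correlation between visits, and the drop-out rate of Section 8.1. It would go beyond the documents to say that the trial wastes much of the precision of these outcomes, since the method for each is not fixed and the correlations are not given. The matter concerns the precision of secondary outcomes only.

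**What to change.** In Section 8.2, state that continuous secondary outcomes with a baseline measurement are compared at each fixed visit (months 6, 12 or 24, as scheduled for that measure) with the participant's baseline value of that measure as a covariate. Use ANCOVA, or a repeated-measures model with arm-by-visit and baseline-by-visit terms. Say that this covers the insulin and OGTT indices, DXA and PWC170. Where the rank analysis is kept, apply it to residuals from a regression on baseline rather than to raw values. Slope comparisons can remain as a supplement where a linear course is reasonable.

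The cost is wording. No new data are needed, the primary analysis does not change, and type I error is not affected if the model is specified before the comparisons are made.

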#### 2.2.5 Nutrition

Hypercaloric, high-fat diets are known risk factors for the development of diabetes, both through promotion of obesity and as an independent risk for insulin resistance. Diet change has been correlated with a decrease in diabetes risk, as well as weight loss, in a number of prevention and intervention studies, including the Diabetes Prevention Program [DPP Research Group 2002]. Therefore, evaluation of baseline diet characteristics, as well as the effect of treatment interventions on dietary change in participants, is considered to be an important secondary outcome of this trial. Diet assessment permits evaluation of the effectiveness of the lifestyle intervention relative to the standard education treatment arms. In addition, dietary assessment over the duration of the trial provides insight into which components of the intervention lead to the most significant and durable change in lifestyle. Such information is critical in translating the results of this study to future trials as well as to clinical practice.

A number of tools can be used to assess dietary intake, a variety of which were considered for this trial. Although there are few validity studies of food frequency approaches in adolescent populations, the available data suggest that validity and reproducibility are comparable to results obtained in adults [Rockett and Colditz 1997]. Recently, the Block Kid's Questionnaire was validated in low-income African-American children. This instrument has been further modified to incorporate common food choices among ethnically and regionally diverse youth aged 10-19 participating in another large childhood diabetes study, SEARCH (SEARCH for Diabetes in Youth, CDC/NIH). Modifications were based on previously validated work with food frequency questionnaire (FFQ) methodology in ethnically diverse populations [Mayer-Davis et al. 1999]. The

instrument is interview-administered and captures the last week of dietary intake. The SEARCH FFQ provides a validated instrument that also enables direct comparisons to the dietary intake of youth with diabetes participating in SEARCH. Dietary assessment is coordinated by the Diet Assessment Center, University of South Carolina, under the direction of [name], from measurements taken at enrollment, six months, two years, primary endpoint, and end of study.

#### 2.2.6 Physical Activity

Physical activity is comprised of activities that span a spectrum of intensity levels and can be assessed using activity recall questionnaires and/or objective measures of activity, such as pedometers and accelerometers. The most popular activity questionnaire currently used with youth is the Previous Day Physical Activity Recall (PDPAR) which involves completion of a questionnaire that assesses the previous days' activities and their relative intensities for the after school hours [Weston 1997]. The PDPAR analyzes the activity level over a short time frame and may not reflect activity levels that vary with seasons or as a result of an acute illness or time commitment [Kriska 1997]. In combination with accelerometer data, it offers a valuable comparison of differential activity levels across treatment arms. The 3-day PDPAR is completed at baseline, 6-months, two years, primary endpoint, and end of study.

One problem with activity recall measures is that lower intensity activities, such as walking, and subtle lifestyle changes, such as taking the stairs instead of the elevator, are harder to recall than higher intensity activities such as organized sports. Therefore, the activity questionnaire may not accurately quantify changes in lower intensity lifestyle activities [Kriska et al. 1990]. The CSA accelerometer allows the collection and storage of daily patterns of physical activity and is a more complex instrument than the pedometer. These monitors have been validated in a variety of laboratory and field settings. In adults, correlation coefficients ranging from  $r = 0.66$  to  $r = 0.89$  between CSA counts and metabolic measures [Melanson and Freedson 1995] have been obtained. In 7-15 year old boys and girls, the CSA was validated against heart rate telemetry with correlation coefficients between the two ranging from  $r = 0.50$  -  $0.74$  [Janz 1994]. Comparisons with oxygen consumption during treadmill exercise and self-selected speed on a track found that the CSA was highly related to both and was highly sensitive to change in speed but not changes in grade [Nichols 2000]. Since the CSA has been found to successfully detect bouts of moderate intensity physical activity such as brisk walking [Masse 1999], this monitor is a good choice for TODAY where moderate intensity activity is the goal. Participants are given an accelerometer to wear at home at baseline, 6 months, two years, primary endpoint, and end of study for 7 days at the time of the PDPAR. Verbal and/or written instructions for the monitors are presented to the child with a diary that needs to be completed on the days that the monitor is worn.

